**Specific Aim 3**: To evaluate the feasibility of the MAHA model.

1)Acceptability by assessing patient and family experience with the program, as well as provider satisfaction2)Utility by examining the actual use of the program and number of referral received by other providers3)Implementation by evaluating the amount and type of resources needed to implement and factors affecting implementation;4)Adaptation by evaluating the selected elements of the program delivered by tele-health is as effective as face-to-face format.5)Financial sustainability and cost saving by comparing the estimated total cost of the program and financial compensation from payers.

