## Methods

### Study design

The study is a prospective, two-group, randomized experimental design with nine data collection points (baseline and every three months). MS patients recruited from a neurology clinic will be randomized into two groups: the intervention or usual care group. The usual care group receives the current standardized MS care, while the intervention group receives usual care plus 24-months of the MAHA intervention provided by a transdisciplinary team led by a MS-Comprehensivist. The usual care group will receive the intervention at the end of the 24-month period if the intervention is found to be effective by our a priori criteria. The study is subject to review and approval by the University of Nebraska Medical Center Institutional Review Board (IRB) and informed consent will be obtained from all participants prior to the study.

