### Data collection, instruments and sources of data

Key data collection instruments, assessments, and measures are summarized in
Table 1. This information will be collected from three data sources: 1) patient reports to CRC personnel, 2) patient reports to the CTL or other MAHA team member at each home visit, and 3) medical record review.

**Table 1. T1:** Study measures.

Data Collection Instrument/Assessment		Method, Location, Data Source	Measure Timeline (in months)								
			BL*	3	6	9	12	15	18	21	24
Kurtzke Expanded Disability Scale (EDSS)		Neurologist/CTL to assess in person	X				X				X
PATIENT REPORTED MEASURES											
-Demographics		CRC to collect at baseline visit and via mail/phone	X								
-Functional activity of daily livings (ADLs) (Barthel) ^42^			X	X	X	X	X	X	X	X	X
-Multiple Sclerosis QoL Inventory (MSQLI) ^43^			X				X				X
-Novak Caregiver Burden Inventory (CBI) ^44^			X	X	X	X	X	X	X	X	X
-Client Satisfaction Questionnaire (CSQ-8) ^45^			X		X		X		X		X
POTENTIAL COMPLICATONS											
-Pneumonia -Urinary Tract Infection (UTI)	-Falls -Pressure Ulcer	CRC to collect at baseline visit, via mail/ phone and from medical record review. Providers assess during in-person visits	X	X	X	X	X	X	X	X	X
HEALTH SERVICES USE											
Emergency Room (ER) -Unplanned (acute)	Inpatient Admissions -Planned (elective) -Unplanned (acute) -Length of Stay	CRC to collect at baseline visit and via mail/phone. Providers assess during in-person visits. Data are retrieved from medical record.	X	X	X	X	X	X	X	X	X
CPT Codes and Reimbursement Amounts		UNMC Neurology Clinic Database	X		X		X		X		X
MAHA RESOURCE INTENSITY											
-Home visit time logs -On-call activity logs -Coordination care management activities		MAHA staff to document after each home visit and on-call activity	X	X	X	X	X	X	X	X	X

**Baseline questionnaires will be performed at the baseline clinic visit*

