***Specific Aim 3.*** To assess the acceptability, utility, implementation and adaptation of the program, we will create a toolkit that comprehensively describes our program structure, processes, patients/provider/system outcomes, as well as lessons learned. This toolkit will serve to evaluate the MAHA program and identify system-, provider-, and patient-levels of barriers and facilitators. To evaluate financial sustainability, we will specifically track the Current Procedural Terminology (CPT) codes for evaluation and management visits (clinic and home visits), care coordination, and care plan oversight. Reimbursement amounts associated with these codes will be summed for each study group at six and 12 months. T-tests and log transformed linear regression models will be used to compare total reimbursement amounts between groups. Also, staffing and associated salary estimates will be computed based on home visit time logs maintained by the MAHA team members, on-call activity logs, and number of home visits in the intervention group. We will project the necessary percent FTE and salary to execute the intervention model based on a range of panel sizes (e.g., 25, 50, 100 patients) per MS-Comprehensivist/CTL. The ratio of total salary costs-to-reimbursement amount for a given number of patients will be calculated for each group and compared using t-tests.

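### Reimbursement is summed at 6 and 12 months in a 24-month programme, so the stated financial comparison covers half the period and gives no use for the month 18 and 24 data

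*Protocol article*

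**What the plan says.** The protocol article deals with the financial question in four places.

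- **Background, Specific Aim 3, item 5.** The aim is "Financial sustainability and cost saving by comparing the estimated total cost of the program and financial compensation from payers". It sets no 12-month limit.
- **Study design.** The "intervention group receives usual care plus 24-months of the MAHA intervention". Usual care patients are offered the programme only after the 24 months, and only if it proves effective.
- **Table 1 (Data collection, instruments and sources of data).** The row "CPT Codes and Reimbursement Amounts" is marked at baseline and at months 6, 12, 18 and 24. The resource logs (home visit time, on-call activity, coordination) are marked at baseline and every quarter to month 24.
- **Data analysis, Specific Aim 3.** "Reimbursement amounts associated with these codes will be summed for each study group at six and 12 months". Then: "T-tests and log transformed linear regression models will be used to compare total reimbursement amounts between groups". Salary estimates are built from the time and activity logs, and finally: "The ratio of total salary costs-to-reimbursement amount for a given number of patients will be calculated for each group and compared using t-tests". Neither of these last two quotations carries a time window.

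**The concern.** The only summation points the article gives for reimbursement stop halfway through the intervention, while its own table continues collecting the same variable to the end. No section calls the 6- and 12-month sums interim, names an 18- or 24-month sum, or explains a 12-month financial horizon.

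Two things are at stake. First, a conclusion about whether a 24-month programme pays for itself would rest on its first 12 months. The second year is still a randomised comparison, because the control group has not yet been offered the programme, so valid comparative data would be left aside. The article describes this phase of the disease as dynamic and bases home visits on individual need, so billing in year 1 cannot simply be assumed to represent year 2.

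Second, the ratio of salary cost to reimbursement has no stated window. Its numerator draws on logs that run to month 24, and the only sums named for its denominator end at month 12. An analyst could combine different periods without departing from the text.

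**Working it through.** The plan states no numerical result on this point, so there is no figure to reproduce. The check compares schedules and then works through the ratio.

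**Inputs**

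| Item | Months | Source in the protocol article |
|---|---|---|
| Length of intervention | 24 | Study design |
| Reimbursement collected | 0, 6, 12, 18, 24 | Table 1 |
| Reimbursement summed for analysis | 6, 12 | Data analysis, Specific Aim 3 |
| Resource logs | 0, then every 3 to 24 | Table 1 |
| Window of the salary-to-reimbursement ratio | not stated | Data analysis, Specific Aim 3 |

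**Step 1: coverage.** The post-baseline collection points are {6, 12, 18, 24} and the points named for analysis are {6, 12}. Those with no named use are {18, 24}, which is 2 of 4. Period covered: 12 / 24 = 50%.

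**Step 2: what a 12-month ratio says about 24 months.** Let S1 and S2 be salary cost in years 1 and 2, and R1 and R2 reimbursement in the same years. The 24-month ratio is

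(S1 + S2) / (R1 + R2) = [R1 × (S1/R1) + R2 × (S2/R2)] / (R1 + R2),

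a weighted average of the two yearly ratios. The 12-month ratio S1/R1 equals it only if S2/R2 is the same as S1/R1. The article gives no figures from which to judge that, so the direction and size of any difference are unknown.

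**Step 3: what happens if the windows differ.** Setting 24-month salary against 12-month reimbursement gives (S1 + S2) / R1. Divided by the matched 24-month ratio:

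[(S1 + S2) / R1] ÷ [(S1 + S2) / (R1 + R2)] = (R1 + R2) / R1 = 1 + R2/R1.

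With constant monthly reimbursement, R2 = R1 and the factor is 1 + 1 = 2. If year 2 reimbursement is lower than year 1 the factor lies between 1 and 2; if higher, it exceeds 2. With constant monthly amounts s and r on both sides, a matched window gives 24s/24r = s/r, and the mismatched one gives 24s/12r = 2 s/r.

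**The case against.** **The text names two points but does not exclude others.** The sentence on the between-group comparison refers to totals without a window, and the aim speaks of the programme's total cost. This stands as a limit on wording: that the second year is left out is the likeliest reading, not an explicit statement. It does not remove the mismatch, because no later sum appears anywhere.

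**A journal article condenses the full protocol.** That would excuse silence on time points. Here the article states them, and they do not fit its own design and table.

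**A 12-month horizon may be deliberate.** It may be, but the article gives no reason for it and no purpose for the month 18 and 24 extractions.

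**The doubled ratio is hypothetical.** This stands. No section sets 24-month salary against 12-month reimbursement. The plan also projects staffing as a percentage of full-time equivalent by panel size, which is a rate that can be applied to any period. Logs running to month 24 therefore do not imply a 24-month numerator. What remains is that the window is unstated.

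**A reader might go further and fault the log-transformed regression**, because it compares geometric means whereas sustainability depends on total payments, and because it cannot take zero totals. The documents do not support making that a finding. The same sentence also plans t-tests, which on the natural reading compare arithmetic means. Any size put on the discrepancy would need log-scale standard deviations that the article does not give, and nothing in it suggests that zero totals would be common among patients of the clinic whose database supplies the amounts. Nor does it describe a start-up phase, so calling year 1 atypical for that reason would be conjecture.

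**Conclusion.** The point holds as an internal mismatch. The stated reimbursement analysis covers 12 of 24 months (50%) and gives no use for 2 of the 4 post-baseline extractions. This rests on reading the two named time points as the whole of the plan, which is the natural reading since no others are given.

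The ratio needs a stated window. A factor of 2 would arise only if 24-month salary were divided into 12-month reimbursement and monthly reimbursement were constant; it is not an effect of the plan as written. Whether the 12-month result would be more or less favourable than the 24-month one cannot be determined from the article.

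The reach is limited to the financial sustainability item of Aim 3. Complications, quality of life, satisfaction and healthcare use under Aims 1 and 2 are untouched.

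**What to change.** In the Data analysis section for Specific Aim 3:

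1. Make the per-patient reimbursement total over the full 24 months the main comparison between groups, and report the cumulative sums at 6, 12 and 18 months as description.
2. State that salary cost and reimbursement in the ratio are both computed over the same 24-month window.

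If a 12-month financial horizon is intended, the alternative is to say so and justify it, apply it to both sides of the ratio, and either give the month 18 and 24 extractions a purpose or align Table 1 with the shorter horizon. The conclusion would then have to be limited to the first year.

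The cost is a change of analysis wording. Reimbursement at months 18 and 24 and the quarterly logs are already scheduled, so no extra patients, visits or data collection are needed.

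### Neither Aim 3 financial test is set against break-even, so neither tests whether payer compensation covers MAHA's cost

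*Protocol article*

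**What the plan says.** The aim is in the Background section of the protocol article, Specific Aim 3, item 5: "Financial sustainability and cost saving by comparing the estimated total cost of the program and financial compensation from payers". That is a question of cost coverage within the program.

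The analysis is in Data analysis, Specific Aim 3, and has three parts.

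- **Reimbursement.** Billing codes for clinic and home visits, care coordination and care plan oversight are tracked. "Reimbursement amounts associated with these codes will be summed for each study group at six and 12 months". Then "T-tests and log transformed linear regression models will be used to compare total reimbursement amounts between groups".
- **Cost.** Staffing and salary are estimated from the MAHA team's home visit time logs, "on-call activity logs, and number of home visits in the intervention group". From these, the staffing and pay that the program would need are projected for several panel sizes, with 25, 50 and 100 patients as examples.
- **Ratio.** "The ratio of total salary costs-to-reimbursement amount for a given number of patients will be calculated for each group and compared using t-tests".

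Under Study design, "the intervention group receives usual care plus 24-months of the MAHA intervention provided by a transdisciplinary team". The MAHA intervention section also expects care at home to spare patients clinic visits.

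**The concern.** The aim asks whether what payers pay covers what the program costs. Both formal tests ask whether MAHA differs from usual care. The first has no cost term. The second has one, but its reference is the usual care ratio and not break-even.

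The abstract already expects the project to be financially sustainable under fee-for-service. If the financial results are reported as p-values from these two tests, a significant excess of reimbursement, or a ratio lower than in usual care, could be taken as confirmation. Either result can occur in a program that loses money.

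**Working it through.** The article gives no financial sample size, margin or break-even figure, so there is no stated number to reproduce. The check is to set each test's null beside the break-even condition.

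**Notation.** R_M and R_U are mean reimbursement per patient under MAHA and usual care; C_M and C_U are the matching salary costs.

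| Item | Quantity | Reference |
|---|---|---|
| Aim 3, item 5 | C_M / R_M (or R_M − C_M) | 1 (or 0) |
| Reimbursement test | R_M − R_U (or difference in mean logs) | 0 |
| Ratio test | C_M / R_M − C_U / R_U | 0 |

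**Reimbursement test.** Take assumed units R_U = 1 and R_M = 2.

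- If C_M / R_M = 0.8, then C_M = 0.8 × 2 = 1.6 and the net is 2 − 1.6 = +0.4.
- If C_M / R_M = 2.0, then C_M = 2.0 × 2 = 4.0 and the net is 2 − 4.0 = −2.0.

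The statistic uses only the reimbursement data, so it has the same distribution in both cases.

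**Ratio test.** Assumed ratios again; the net per unit reimbursed is 1 minus the MAHA ratio.

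- MAHA 1.25, usual care 2.0: MAHA looks better, yet the net is 1 − 1.25 = −0.25.
- Both 1.25: the null is true and MAHA loses 0.25.
- Both 0.8: the null is true and MAHA gains 1 − 0.8 = 0.2.

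A difference, or its absence, does not place MAHA on either side of 1. A usual care ratio also needs C_U, and the cost logs named record MAHA activity only.

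**Illustration of the reimbursement test.** Assumptions: lognormal patient totals, coefficient of variation (CV) 0.5 or 1.0, two-sided 5% level, 4,000 simulated trials per case. Both 25 and 50 per arm are shown because the abstract gives fifty patients in total and the Sample size section gives 50 per group. Entries are rejection rates for the t-test, with the log-scale test in brackets.

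| R_M / R_U | 25 per arm, CV 0.5 | 25 per arm, CV 1.0 | 50 per arm, CV 0.5 | 50 per arm, CV 1.0 |
|---|---|---|---|---|
| 1.0 | 0.05 (0.05) | 0.04 (0.05) | 0.04 (0.04) | 0.05 (0.05) |
| 1.5 | 0.82 (0.85) | 0.30 (0.39) | 0.98 (0.99) | 0.55 (0.68) |
| 2.0 | 1.00 (1.00) | 0.70 (0.82) | 1.00 (1.00) | 0.94 (0.99) |
| 3.0 | 1.00 (1.00) | 0.96 (1.00) | 1.00 (1.00) | 1.00 (1.00) |

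The rates depend on how far billing differs and how variable it is. They do not depend on program cost.

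**The case against.** The strongest reply is that the plan does bring cost and compensation together. It estimates salary, projects it to several panel sizes, and calculates a salary cost-to-reimbursement ratio for each group. A MAHA ratio above 1 would show salary exceeding reimbursement to anyone who looked. This stands. A reader might infer that sustainability is judged on reimbursement alone, and the text does not support that. What remains is that the ratio's planned test also compares arms, not MAHA with 1.

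A reader might also infer that the reimbursement test must reject because home visits are billed on top of usual care. The documents do not support that either. They expect clinic visits to be avoided, so the net difference in billing is unknown; with full substitution and equal fees, rejection is about 5%.

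Nor are the high rejection rates inflated type I error. They are ordinary power to detect a real difference in reimbursement. The article never states unsustainability as the null of that test and ties no sustainability decision to its p-value.

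Item 5 also names cost saving, for which a comparison between arms is a natural component. That is a reason to keep the comparison, not to read it as cost coverage.

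Finally, a break-even threshold or decision rule could sit in a fuller document. Its absence is not the point here: the article names its tests, and both have a reference that differs from its own aim.

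**Conclusion.** The point holds in limited form. The plan collects and combines the right quantities, but neither formal financial test addresses the question in Aim 3, item 5. A significant reimbursement difference cannot separate a self-funding program from a loss-making one. A difference in the ratio between arms cannot do so either, and the source of the usual care cost is unclear.

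This conclusion follows from the nulls and needs no assumed number. Its practical size cannot be derived, because the documents give no dollar, visit or variance figures; the simulated rates rest on assumed inputs and are illustrative only. Here cost means salary, as in the plan's ratio, whereas item 5 speaks of total program cost. The matter affects one component of the feasibility aim and leaves Aims 1 and 2 untouched. It is worth correcting because the change is cheap.

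**What to change.** 1. Report the between-arm reimbursement difference with a confidence interval as a description of billing, and do not offer its p-value as evidence of sustainability.
2. Base the sustainability conclusion on the MAHA-arm salary cost-to-reimbursement ratio, with a 95% confidence interval set against 1, or on reimbursement minus program cost set against 0. A bootstrap over patients would serve. It also gives an interval for a ratio of group totals, which a t-test cannot do from one number per arm.
3. Show the result for each projected panel size (25, 50, 100), since staffing cost per patient may change with the panel.
4. If an incremental contrast is added, credit clinic staff cost saved (S) where home visits replace clinic visits: (R_M − R_U) − (C_M − S). Without S, full substitution penalises a program that pays its way. With R_M = R_U = 1 and C_M = 0.8, the contrast is 0 − 0.8 = −0.8, although MAHA billing exceeds MAHA salary by 1 − 0.8 = 0.2.

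Table 1 already schedules the reimbursement amounts and MAHA time logs that steps 1 to 3 need. The cost is revised wording and a little more analysis; S in step 4 would need an estimate of clinic staff cost. The downside is a sustainability claim that is harder to meet.

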### Sample size

The sample size estimation is computed based on
**Specific Aim 1**: the increased score of quality of life (QoL) and
**Specific Aim 2**: the reduced number of unplanned healthcare utilizations associated with complications. An estimated 50 patients per group will provide 80% power to detect a 5-point difference [Usual Care mean (SD): 45(8.6), MAHA mean (SD) 50(8.6)] between groups in the SF-36 Mental Health Component Score QoL. This sample size also provides 80% power at a 5% significance level to detect a 34% reduction in unplanned visits/admits (from 2.5 per person per year to 1.65, using the Poisson distribution, which is most appropriate for count/rate data). These are feasible and clinically important differences. Based on our preliminary analyses, 125 patients are currently expected to meet these criteria. Furthermore, based on our previous patient survey results, a high proportion of patients (~80% or n = 100) have expressed a genuine interest in participating in MS research for the benefit of others with this disabling disease. Furthermore, we estimate 50 patients will be a reasonable panel size for the MS-Comprehensivist or care team leader (CTL) in the MAHA model (unpublished report).

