### Data analysis

***Specific Aim 1 and 2.*** The data analysis will follow the intention-to-treat (ITT) protocol. To ensure groups are comparable, descriptive analyses, including t-tests and Chi-square tests will be conducted to compare the characteristics of each group at baseline. The occurrence of complications and other self-reported measures, such as ADLs, Multiple Sclerosis QoL Inventory (MSQLI), CSQ-8, and Caregiver Burden Inventory (CBI) will be compared between groups using a linear mixed model to account for the repeated measurements over time and adjust for baseline scores of the respective measures. To determine if differences exist between groups after adjusting for potential confounding variables, such as age, gender, comorbidity, etc. or imbalances between groups, unplanned healthcare utilization (i.e., visits/admissions) will be analyzed using Poisson regression models. The proportion of any versus no use of each health service (e.g., proportion with any inpatient admissions versus the proportion with no admissions) will be compared between groups using Chi-square tests. The time-by-group interaction will be investigated to determine if any changes over time are consistent between groups.

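### The t-test of total reimbursement cannot use the baseline reimbursement already scheduled for collection, and the plan does not say whether the log-transformed regression does

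*Protocol article*

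**What the plan says.** Protocol article, Data analysis, Specific Aim 3: billing codes for visits, care coordination and care plan oversight are tracked. Then "Reimbursement amounts associated with these codes will be summed for each study group at six and 12 months", and "T-tests and log transformed linear regression models will be used to compare total reimbursement amounts between groups". No covariate is named for either method.

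Protocol article, Data collection, Table 1: the row "CPT Codes and Reimbursement Amounts", taken from the clinic database, is marked at baseline and at 6, 12, 18 and 24 months.

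Protocol article, Data analysis, Specific Aim 1 and 2: complications and self-reported measures go into a linear mixed model chosen to "account for the repeated measurements over time and adjust for baseline scores of the respective measures". Unplanned utilisation goes into Poisson regression "after adjusting for potential confounding variables, such as age, gender, comorbidity, etc. or imbalances between groups".

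Protocol article, Study design: the trial is a "prospective, two-group, randomized experimental design with nine data collection points". The Abstract mentions block randomisation; the article states no stratification on earlier billing or service use.

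**The concern.** A baseline value of the outcome is often one of its better predictors. Here it is due to be collected, yet one of the two named methods cannot use it and the other is not said to. The same section writes baseline adjustment for the Aim 1 measures, so the difference in treatment is visible within the article.

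At stake is the precision of the planned between-group comparison of reimbursement, which supports the financial sustainability part of Aim 3. If a patient's earlier billing predicts later billing, the unadjusted comparison leaves explainable variation in the error term. The interval is then wider than the scheduled data would allow. The trial is small, so chance differences in earlier billing between the groups may also be large enough to complicate reading the result.

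**Working it through.** **The plan's own figures.** The article gives no power, SD, target difference or precision for reimbursement, so there is no figure of its own to reproduce on this point. Its general sample size can be checked. The Sample size section states "An estimated 50 patients per group will provide 80% power to detect a 5-point difference", with SD 8.6. Two-sided 5% is assumed, since sidedness is not stated. Then n = 2 × (1.960 + 0.842)² × 8.6² / 5² = 46.4, so 47 per group, and 50 per group gives about 83% power. The stated size is reproduced, but it says nothing about reimbursement.

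**Inputs for this point.**
- Patients per group: 50 (Sample size section). The Abstract gives fifty patients in all, which would be 25 per group if split equally, so both are shown.
- Correlation r between baseline and follow-up reimbursement within group: not in the article. Assumed at 0.2, 0.3, 0.5 and 0.7.
- Effect: not in the article. Set to whatever the t-test would detect with 80% power.

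**Formulas.**
- Variance of the adjusted difference relative to the t-test: 1 − r².
- Interval width ratio: √(1 − r²).
- Adjusted power: Φ[(1.960 + 0.842)/√(1 − r²) − 1.960].
- Detectable difference in SD units: 2.802 × √(2/n) × √(1 − r²). Unadjusted this is 2.802 × 0.200 = 0.56 at 50 per group and 2.802 × 0.283 = 0.79 at 25 per group.

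| r | Variance cut | Width ratio | Power (80% unadjusted) | Detectable difference, 50 per group | Detectable difference, 25 per group |
|---|---|---|---|---|---|
| 0.2 | 4% | 0.980 | 81.6% | 0.55 | 0.78 |
| 0.3 | 9% | 0.954 | 83.6% | 0.53 | 0.76 |
| 0.5 | 25% | 0.866 | 89.9% | 0.48 | 0.69 |
| 0.7 | 49% | 0.714 | 97.5% | 0.40 | 0.57 |

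Example at r = 0.5: 2.802/0.866 = 3.235; 3.235 − 1.960 = 1.275; Φ(1.275) = 0.899.

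Repeating this with the noncentral t distribution, one degree of freedom removed and 50 per group, gives 81.6%, 83.6% and 89.9% at r = 0.2, 0.3 and 0.5. At r = 0.35 it gives 84.9%, so the gain reaches about 5 percentage points there.

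**Is the unadjusted t-test valid?** In 20,000 simulated trials per setting, with normal data, no true effect, r = 0.5 or 0.7 and 25 or 50 per group, the type I error was 4.8% to 5.0% and the mean difference was about zero. The chance baseline difference has standard error √(2/n), which is 0.20 SD at 50 per group and 0.28 SD at 25. A fraction r of it carries into the unadjusted difference. Among only those trials whose baseline difference exceeded 1.96 standard errors, the false-positive rate was about 17% to 20% at r = 0.5 and 32% to 33% at r = 0.7. Such trials are about 1 in 20, and the overall error rate already includes them.

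**The case against.** **The regression may already be adjusted.** A reader might infer that neither method has a baseline term. The article does not support that. It lists no covariates for the log-transformed regression and never calls it unadjusted. A two-group regression without covariates would only repeat a t-test on logs, so naming it separately may well imply adjustment. A condensed article may leave the covariate list to the full protocol or SAP. This stands, and only the t-test is certain to ignore baseline.

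**The t-test is valid.** A reader might also infer that chance differences in earlier billing bias the comparison. They do not: randomisation and the standard error cover them, as the simulation shows. This stands too, and leaves a loss of efficiency.

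**The correlation may be low.** The outcome covers a narrow set of codes from one clinic. In the intervention group, home visits on a new schedule could weaken the link with earlier billing. This is plausible, and the article gives nothing to settle it.

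**Baseline is not defined.** No billing window is given, and Table 1 also marks baseline for the MAHA activity logs, so the mark alone does not establish a pre-randomisation total. This is fair and means the fix must define the window. The amounts come from a clinic database, which could supply a common look-back.

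**The comparison is supporting evidence.** Aim 3 judges sustainability mainly by setting programme cost against payment, and the trial is sized on other outcomes. This limits the importance of the point but does not remove it.

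**Conclusion.** The point holds as a modest one about efficiency. The named t-test cannot use a baseline value that the plan schedules, and the role of that value in the regression is left unsaid, while the same section adjusts the Aim 1 measures for baseline. It is not an invalid analysis or a bias.

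The gain from adjustment runs from negligible at a correlation of 0.2 to about half the variance at 0.7. It is small below about 0.35. These figures rest on an assumed correlation common to both groups, on the scale analysed, and on a baseline total that can be defined alike for everyone. In relative terms the gain is essentially the same at 25 or 50 per group.

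The article writes of amounts summed by study group, but a t-test needs one value per patient, so a patient-level baseline covariate fits the planned analysis.

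**What to change.** In Data analysis, Specific Aim 3:
- make the between-group comparison of total reimbursement a regression of each patient's follow-up total on study group and that patient's baseline reimbursement;
- state that the planned log-transformed model contains the same baseline term;
- keep the t-test as descriptive only;
- define baseline reimbursement with the same look-back length for every patient.

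The cost is one degree of freedom (98 to 97 at 50 per group, 48 to 47 at 25), a short change of wording, and the work of fixing and extracting a common look-back window. The row and its database source are already in Table 1. If the full protocol or SAP already includes baseline reimbursement in the regression, what remains is to say so and to name that model as the comparison. The choice between the dollar and log scales, and of standard errors, is a separate matter that this point does not decide.
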